### Sample size calculation

The required sample size has been calculated according to the guidelines of the Consolidated Standards of Reporting Trials (also known as CONSORT) for cRCTs [59], considering the intraclass correlations of the outcomes nested by the worksites. The sample sizes in cRCTs should be multiplied by the design effect (1 + [m-1]ρ), where m is the average cluster size and ρ is the intraclass correlations [60]. In the dataset from a cohort of healthy Japanese workers [61, 62], the intraclass correlation for depression and anxiety measured by the K6 scale was 0.013. Therefore, a very small intraclass correlation (0.05, 5% of the outcome would be shared at the worksite level) was estimated for the primary outcome in this study. The average cluster size (the number of employees within one worksite) was set to 130 based on the information about potentially recruiting 2,700 companies from IID Co. Ltd.

The effect size of the four intervention programs on the primary outcome, that is, depression and anxiety, was estimated to be 0.20 in the standardized mean difference (d). A previous RCT that offered an Internet-based cognitive behavioral approach to prevent depression among nonclinical workers reported the effect size (d) of the intervention as 0.20 at the 6-month follow-up [63]. The effect sizes of work environment improvement and physical activity promotion on mental health among nonclinical workers were reported to be larger [35, 64]. An alpha error probability (α) has been set to 0.05/4 = 0.0125 (one-tail) because we plan four tests between the intervention programs and control programs. The statistical power (1-β) has been set to 0.80.

Based on these parameters, the required sample size has been calculated as 3,554 for each arm using G* Power version 3.1.9.2 [65]. Considering that the average number of employees within one worksite is assumed to be 130, 27.3 worksites will be needed in each arm. Therefore, we have set the required number of worksites and employees to 28 and 3,640 in each arm and to 140 and 18,200 in total.

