The required number of worksites (140) is 5.2% of the recruited companies (2,700). Previous RCTs on nonclinical workers at multiple worksites in Japan reported acceptance rates of approximately 4% [63, 66]. In this cRCT, the acceptance rate is likely to be higher and to reach the target sample size by prioritizing the recruitment of stressful worksites, which may in turn require countermeasures for stress management.

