### Statistical analysis

For the main analysis, repeated-measures multi-level mixed modeling will be used to test the effects of each intervention compared with the control at the 6-, 12-, and 18-month follow-ups. The interaction effect of the group (1 = intervention, 0 = control) by time will be considered an indicator of the intervention effect. The multi-level is based on employees (level 1) and worksites (level 2). The variables used in the stratified randomization (i.e., worksite size, industries, and the percentage of “high-stress” employees in the worksites) will be used as covariates. Intention-to-treat analysis will be adopted by including all employees who completed the baseline survey in the analysis. Multiple imputations will be conducted for missing values owing to dropouts. Effect sizes will be calculated as the standardized mean differences (d) of the scores on the K6 scale, based on the estimated mean differences.

The primary endpoint of the primary outcomes is set at the 6-month follow-up, and the corresponding statistical significance will be the primary indicator of effectiveness. If recruitment does not achieve the target sample size (140 worksites and 18,200 employees in total), we will assess the intervention effectiveness based on a minimally important difference. As the estimated effect size of the interventions is 0.20, the distribution-based approach [67] is useful for estimating the minimally important difference of depression and anxiety measured by the K6 scale. In a previous RCT among nonclinical workers in Japan [63], the standard deviation of the change in the K6 score at the 6-month follow-up was 4.16. From the distribution, 20% of the standard deviation is estimated to be 0.832. Therefore, a 0.85 score change in the K6 score at the 6-month follow-up is considered to be the minimally important difference.

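### Any recruitment shortfall moves the effectiveness criterion from 6-month significance to a 0.85-point K6 threshold with no error rate attached; read as a point-estimate rule, it passes the planned effect less than half the time

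*Protocol article*

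**What the plan says.** The Statistical analysis section of the protocol article fixes a repeated-measures mixed model with a group-by-time contrast against control. At the 6-month primary endpoint, "the corresponding statistical significance will be the primary indicator of effectiveness".

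The next sentence sets a condition: "If recruitment does not achieve the target sample size (140 worksites and 18,200 employees in total"), then "we will assess the intervention effectiveness based on a minimally important difference". The threshold is built in two steps. From an earlier trial, "the standard deviation of the change in the K6 score at the 6-month follow-up was 4.16", and "20% of the standard deviation is estimated to be 0.832". The section then concludes that "a 0.85 score change in the K6 score at the 6-month follow-up is considered to be the minimally important difference". It attaches no alpha, confidence bound or multiplicity rule to this criterion.

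The Sample size calculation section plans on d = 0.20, one-tailed alpha 0.05/4 = 0.0125, power 0.80, an intraclass correlation (ICC) of 0.05 and 130 employees per worksite. It arrives at 3,554 employees per arm and then "set the required number of worksites and employees to 28 and 3,640 in each arm". The same section puts the required 140 worksites at 5.2% of the 2,700 companies approached. It cites earlier acceptance of about 4% and expects to do better by prioritising stressful worksites.

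**The concern.** The standard for calling a programme effective depends on how many worksites are recruited. At target it is a test with a stated error rate. Below target, by however little, it is a fixed number of K6 points with no reference to sampling error.

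The number chosen is the effect on which the trial is planned, rounded up. Using that value to interpret an interval is ordinary practice. Using it as a pass mark for an estimate is different: an estimate centred just below the mark falls short of it slightly more often than not, however large the trial. The fallback would then give away most power where the planned test still works well, and the chance of passing an ineffective programme would drift with recruitment. This rule would govern the primary conclusion for all four comparisons.

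The trigger is realistic. Four per cent of 2,700 is 108, against 140 needed. The employee target is 140 × 130 = 18,200, where 130 is the average number of employees in a worksite. It therefore assumes that every one of them takes part, although the article excludes some employees and allows others to refuse.

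**Working it through.** **Inputs.** From Sample size calculation: d = 0.20, one-sided alpha 0.0125, power 0.80, ICC 0.05 (0.013 in the cited cohort), cluster size m = 130. From Statistical analysis: SD of K6 change 4.16, threshold 0.85. From Trial design: equal allocation to five arms.

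**Step 1: the plan's own figures.** A two-sample t-test with d = 0.20, one-sided 0.0125 and power 0.80 needs 477 per arm. The design effect is 1 + 129 × 0.05 = 7.45, and 477 × 7.45 = 3,553.65, which rounds up to 3,554 as stated. Then 3,554/130 = 27.3 worksites, set to 28. The planned effect in K6 points is 0.20 × 4.16 = 0.832, as stated; 0.85 is 0.85/4.16 = 0.204 SD.

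**Step 2: formulas.** Let n be employees per arm and DE the design effect, and express improvement against control as a positive number.

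- SE = 4.16 × √(2 × DE/n)
- Fallback rule, read as estimated difference from control ≥ 0.85: P(pass) = Φ((true effect − 0.85)/SE)
- Planned test: power = Φ(0.832/SE − 2.241), where 2.241 is the normal quantile for one-sided 0.0125

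Example at 108 worksites: n = 21.6 × 130 = 2,808 and SE = 4.16 × √(14.9/2,808) = 0.303. The rule passes the planned effect with probability Φ(−0.018/0.303) = 0.476. The test has power Φ(2.746 − 2.241) = 0.69. With no effect, the rule passes with probability Φ(−0.85/0.303) = 0.0025.

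**Step 3: results at ICC 0.05.**

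| Worksites in total | SE | Planned test, power at 0.832 | Rule, pass at 0.832 | Rule, pass at zero effect |
|---|---|---|---|---|
| 140 (for reference) | 0.266 | 81% | 47.3% | 0.07% |
| 135 | 0.271 | 79.6% | 47.4% | 0.09% |
| 108 | 0.303 | 69% | 47.6% | 0.25% |
| 80 | 0.352 | 55% | 48.0% | 0.79% |
| 70 | 0.376 | 49% | 48.1% | 1.2% |
| 50 | 0.445 | 35% | 48.4% | 2.8% |

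Because 0.832 is below 0.85, the pass rate stays under 50% at every size. A simulation with 22 worksites per arm gave 47.7% at the planned effect and 0.24% at zero effect.

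**Step 4: where the error rate crosses the planned level.** The rule's false-positive rate equals 1.25% when SE = 0.85/2.241 = 0.379. That is n = 14.9 × (4.16/0.379)², about 1,793 per arm, or about 69 worksites in total. Above that number the rule is stricter than the planned test; below it, more lenient.

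**Step 5: sensitivity.**

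- ICC 0.013 (DE = 2.677): at 108 worksites the test has 99% power and the rule passes 46%. The crossing point falls to about 25 worksites.
- Larger true effects at 108 worksites, ICC 0.05: d = 0.25 passes 74% and d = 0.30 passes 91%.
- A different SD behind d = 0.20 (assumption): 0.20 SD exceeds 0.85 once the SD is above 4.25. At 108 worksites, SD 4 gives 43% and SD 5 gives 66%.

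**The case against.** The strongest reply is that the article never says the test is dropped or that a bare estimate is compared with 0.85. The mixed model remains, the fallback is specified in advance, and it depends on recruitment rather than on outcomes. How the minimally important difference is applied could sit in an analysis plan that is not shown. This has weight: the pass rates above depend on the point-estimate reading. It does not remove the point, because the article itself states the switch, its trigger and its number. Requiring a confidence bound to clear 0.85 would pass the planned effect less often still.

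Four stronger readings are tempting and are not supported.

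- **That the rule inflates false positives in any short trial.** With the protocol's cluster size it is stricter than planned down to about 69 worksites, roughly half the target.
- **That any effective programme fails more often than not.** The figure of 47–48% belongs to an effect of exactly 0.832 points. The sample size section says that work environment improvement and physical activity promotion had larger reported effects, and such effects would pass more often.
- **That the fallback is almost certain to be used.** The article expects acceptance above 4%. The figure of 108 also equates companies with worksites, as the article does, yet a company supplies a list of worksites and may contribute several.
- **That 0.85 is a change within an arm.** The wording leaves this open, but the same section defines the effect as a group-by-time contrast with control, so the between-arm reading is the natural one. One clarifying phrase is enough.

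**Conclusion.** The concern holds as a flaw in the stated decision rule for the primary conclusion. On any shortfall, effectiveness is to be judged against a threshold of 0.85 points, just above the planned effect of 0.832, with no error rate specified.

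Near target the loss is power: for a programme with exactly the planned effect, from about 80% to 47% at 135 worksites and from 69% to 48% at 108. With ICC 0.013 the contrast at 108 worksites is 99% against 46%. Excess false positives are a secondary matter, confined to trials below about 69 worksites at ICC 0.05.

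These figures assume that the rule is applied to the estimated difference from control, that clusters are equal at 130 with no attrition, and that SD 4.16 and the stated ICC apply to the difference in change. That a shortfall would be met by this rule follows from the text; that a shortfall will occur is only plausible.

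**What to change.** Remove the switch. Use the same 6-month group-by-time contrast, at the same multiplicity-adjusted level, whatever number of worksites and employees is reached. Report the between-arm difference in K6 with its confidence interval for each programme. State that the minimally important difference is a between-arm difference, and use it only to interpret that interval.

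This costs one paragraph of protocol or analysis-plan wording and a registry update. It needs no extra data or worksites. It should be settled before the 6-month outcomes are analysed. The downside is that a short trial must openly report its reduced power, for example 69% at 108 worksites or 55% at 80 under ICC 0.05.

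### The fallback K6 threshold of 0.85 points is 0.018 above the 0.832 that its own derivation gives, and no reason is stated (minor)

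*Protocol article*

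**What the plan says.** The passage is in the protocol article, Statistical analysis, second paragraph. The primary indicator of effectiveness is significance at 6 months. If 140 worksites and 18,200 employees are not reached, effectiveness is judged against a minimally important difference in K6. The derivation has four steps:

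- The starting point is the design effect size: "As the estimated effect size of the interventions is 0.20, the distribution-based approach [67] is useful for estimating the minimally important difference".
- The spread comes from an earlier RCT in nonclinical Japanese workers (reference 63), where "the standard deviation of the change in the K6 score at the 6-month follow-up was 4.16".
- The product: "From the distribution, 20% of the standard deviation is estimated to be 0.832".
- The conclusion: "Therefore, a 0.85 score change in the K6 score at the 6-month follow-up is considered to be the minimally important difference".

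The Sample size calculation section gives the design effect for the primary outcome, which "was estimated to be 0.20 in the standardized mean difference (d"), and supports it with the same earlier RCT.

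**The concern.** The last step is worded as an inference from the one before it, but the number changes on the way. Ordinary rounding of 0.832 gives 0.83. The value 0.85 results only from rounding to the nearest 0.05, a rule that the article does not mention, and no clinical or anchor-based reason is offered for the higher figure.

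This would be cosmetic if the number were only descriptive. Here it serves as the criterion of effectiveness in the fallback. The fallback is a realistic case on the article's own figures: the recruitment paragraph needs 5.2% acceptance and cites about 4% in earlier trials, although the authors expect to do better. An estimate between 0.832 and 0.85 would meet the stated derivation and fail the stated threshold. That ambiguity should be settled before anyone sees the data. The direction is also fixed, because the higher figure always makes it harder for a programme to be called effective.

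**Working it through.** **Inputs from the article.** Multiplier 0.20, SD of change 4.16, stated product 0.832 and stated threshold 0.85 (Statistical analysis). ICC 0.05 for design and 0.013 in the cited cohort, average worksite size 130, and 28 worksites per arm (Sample size calculation). About 4% acceptance among 2,700 companies (the paragraph after the sample size).

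**Step 1: reproduce the derivation.** 0.20 × 4.16 = 0.832. The intermediate figure is correct.

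**Step 2: compare with the stated threshold.**

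- 0.85 − 0.832 = 0.018 K6 points.
- 0.85 / 0.832 = 1.022, so the threshold is 2.2% higher.
- 0.85 / 4.16 = 0.204 SD of change, against 0.20.

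**Step 3: effect on the decision.** Assumptions: the point estimate is compared with the threshold (the article does not say whether a confidence limit is meant), the SD of change is 4.16 in each arm, the ICC applies to change, all worksites have 130 employees with complete data, and the estimate is approximately normal.

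- Design effect: 1 + 129 × ICC, which is 7.45 at ICC 0.05 and 2.677 at ICC 0.013.
- SE of the difference between two arms: 4.16 × √(2 × design effect / (k × 130)), with k worksites per arm.
- Chance of reaching 0.85 when the true effect is 0.832: P(Z > 0.018 / SE).

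The lower value of k takes 4% acceptance with one worksite per company: 0.04 × 2,700 / 5 = 21.6 per arm.

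| k per arm | ICC | SE | 0.018 / SE | Chance of reaching 0.85 |
|---|---|---|---|---|
| 28 | 0.05 | 0.266 | 0.068 | 47.3% |
| 28 | 0.013 | 0.160 | 0.113 | 45.5% |
| 21.6 | 0.05 | 0.303 | 0.059 | 47.6% |
| 21.6 | 0.013 | 0.182 | 0.099 | 46.1% |

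With a threshold of 0.832 the chance is 50% in every row. The loss is therefore 2.4 to 4.5 percentage points. The rows with 28 worksites mark the upper boundary: the worksite target is then met, and the fallback would apply only if the number of employees fell short.

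**Step 4: no true effect.** With half the planned size (1,820 per arm, ICC 0.05) the SE is 0.376. The chance of an estimate at or above the threshold is 1.20% at 0.85 and 1.35% at 0.832. The difference is negligible.

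The planned sample size is untouched, because it rests on d = 0.20 and does not use 0.85.

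**The case against.** **The gap is trivial and in plain view.** The article prints 0.832 next to 0.85. The difference is 0.018 points on a total that runs from 0 to 24, and the implied d is still 0.20 to two decimals. A minimally important difference need not equal the design effect exactly. This largely stands, and it is why the point is minor. It does not remove the point, because a prespecified decision threshold that is presented as following from a calculation should equal its result or carry a reason.

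**A reader might infer that the higher figure makes a programme that works exactly as assumed fail.** That is too strong. A threshold equal to the true effect is missed half the time in any case; the step to 0.85 adds only the few percentage points shown in the working.

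**A reader might also infer a mismatch of scales,** because the article says "Effect sizes will be calculated as the standardized mean differences (d) of the scores on the K6 scale" while the threshold uses an SD of change. The documents do not support this:

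- The quoted sentence concerns effect sizes to be reported and names no standardizing SD.
- The Sample size calculation section does not say which SD lies behind 0.20. It says that the earlier RCT "reported the effect size (d) of the intervention as 0.20 at the 6-month follow-up [63"], and that RCT is also the source of the 4.16.
- The tested effect is the group-by-time interaction, which is a difference in change, so an SD of change is a coherent choice.
- If score variances are equal at both times, the two SDs coincide at a baseline-to-6-month correlation of 0.5. The article gives neither that correlation nor the SD of scores, so neither a discrepancy nor its direction can be shown.

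**Conclusion.** The point holds as a minor arithmetic inconsistency: the derivation gives 0.832 and the threshold is stated as 0.85 without a reason. It matters only in the fallback, and only for estimates in or near that narrow band. The probabilities depend on the assumptions in the working, chiefly that the point estimate is what is compared with the threshold. The gap of 0.018 points needs no assumption. No error is claimed in the multiplier, the choice of SD, the product or the sample size.

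**What to change.** In the Statistical analysis section, state the minimally important difference as 0.832 K6 points (or 0.83, its two-decimal rounding), and make the change before the results are known. Keeping 0.85 would require a sentence giving the reason for it. The cost is one number in one sentence; the design, sample size, data collection and analysis model stay as they are.

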### Data monitoring

A data monitoring committee will be established comprising the corresponding author (KW), the manager of enrollment (KY), and intervention program providers (AS, KI, TY, KW, and AI). The data monitoring committee meeting will be held every six months, in line with the surveys. The purpose of the meetings will be to review the recruitment process, program completion rates, attrition rates, and any harm caused by the interventions.

## Ethics and dissemination

### Ethical considerations

The study protocol was approved by the Research Ethics Committee of the Kitasato University Medical Ethics Organization, Japan (C22-082). Informed consent will be obtained from representatives of the worksites when a company agrees to participate in the study. In the baseline survey, consent from employees will also be obtained via paper-signed or online forms. If eligible employees in the participating worksites refuse to join the study, we will not include them in the study but will allow them to be offered interventions. The obtained data will be stored on a standalone computer at the Department of Public Health, Kitasato University School of Medicine, and managed by an independent research assistant. The data will not be anonymized and shared with the intervention program providers within the research team on request when the implementation data are analyzed or reminders and feedback with letters of gratitude are sent. The research ethics committee approved the data management plan.

### Dissemination of research findings

The results and findings will be submitted and published in a peer-reviewed scientific journal according to the Consolidated Standards of Reporting Trials guidelines for cRCTs [59]. The results will also be provided to the participating worksites and employees. If the effectiveness and implementation outcomes are significant and promising, intervention programs will be packaged by private vendors in Japan and disseminated to companies that do not participate in the study.

### Strengths and limitations

This study will be the first cRCT with a large sample size, multiple arms, and long follow-up period to investigate the effect of primary preventive interventions on depression and anxiety in occupational health. The results and findings from the 140 worksites and 18,200 employees will be generalizable to other worksites in Japan. Moreover, the multiple-arm and outcome-wide study design will enable us to compare the effectiveness of the four interventions on broad outcomes simultaneously, with the same control group. Therefore, the results and findings will establish a model to present the scientific evidence and support the decision-making of employers for future primary preventive approaches.

This study will have several limitations. In the long follow-up period, some employees and some worksites will likely be removed from the study. Although we will adopt intention-to-treat analysis and plan to impute the missing values at the analysis phases, too much attrition will cause selection bias. Moreover, as the primary outcomes, depression and anxiety, will be measured using a self-reported scale, the results for the effectiveness of the programs will contain certain measurement errors and information bias. Furthermore, the randomization of the five arms will be conducted under various strata, meaning that even if a large pool of worksites is included, successful randomization depending on recruitment cannot be guaranteed.

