Researchers have extensively reported on the effectiveness of primary (proactive) preventive interventions for mental health conditions [15, 16]. Prior research often applied these interventions at the organizational level to combat major causes of depression and anxiety (e.g., poor psychosocial work environment) among workers [17–19]. There are also systematic reviews on participatory organizational interventions focusing on job design and workload and break changes [20, 21]. Training for supervisors is important in improving their knowledge, attitudes, and behaviors to provide support for their subordinates [22], and academicians have conducted individual-focused interventions to enhance workers’ skills, tolerance, and resilience. The effects of cognitive behavioral techniques, such as mindfulness and cognitive behavioral therapy, or physical activity interventions, such as walking, yoga, resistance training, and aerobics, have been described [16, 23]. Accordingly, a combination of organizational- and individual-focused interventions have been proposed for the effective management of mental health [15, 24].

However, the scientific evidence on these interventions remains limited because of the lack of controlled trials, especially cluster randomized controlled trials (cRCT) [1, 25]. This lack of cRCTs leaves unclear the effects of these interventions, including organizational changes and organizational-level process and implementation outcomes such as feasibility and acceptability [1]. The impact of these interventions on physiological and economic outcomes, such as biomarkers and work performance, also remains underexplored [26]. Further, most previous studies had a short follow-up period; therefore, the long-term impact of the interventions and their sustainability is still unknown [27]. Another research gap relates to the low comparability among interventions. As previous studies have evaluated the preventive effects of each intervention separately in different samples, the most effective intervention has not been identified. These research gaps may lead to ambivalence in employers’ decision-making for choosing appropriate interventions. To address these research gaps, a multi-arm cRCT study with a long follow-up period is needed.

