### Objectives

To address these research gaps, the present study aims to assess the effects of four types of organizational interventions on the prevention of depression and anxiety among workers. Non-specific psychological distress will be used as an indicator of depression and anxiety. The interventions include psychoeducation for workers and supervisors, work environment improvement, and promotion of physical activity. The intervention programs contain Internet-delivered or smartphone-delivered content using information communication technologies. As secondary outcomes, the effects on psychosocial factors at work, work engagement, health-related QOL, well-being, economic outcomes, physiological outcomes of a health checkup, and cortisol levels extracted from fingernails will also be identified. Further, the process and implementation outcomes of the intervention programs will be evaluated for their future dissemination in workplaces. Follow-up surveys will be conducted at 6, 12, and 18 months from baseline. The primary hypothesis for this study is that depression and anxiety will significantly improve or be maintained in the four intervention worksites at the primary endpoint (i.e., six months after the baseline) compared with those in active control worksites.

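### The article presents the trial as comparing the four programmes to help employers choose, but every planned effectiveness analysis is against control, so differences between programmes get no measure of uncertainty

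*Protocol article*

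**What the plan says.** **What is promised.** The Background lists low comparability between interventions as a research gap. It says that "the most effective intervention has not been identified" and links this to employers' difficulty in choosing. It then concludes: "To address these research gaps, a multi-arm cRCT study with a long follow-up period is needed". The Strengths and limitations section says that the "study design will enable us to compare the effectiveness of the four interventions on broad outcomes simultaneously, with the same control group", and that the findings will "support the decision-making of employers for future primary preventive approaches".

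**What is planned for effectiveness.**
- Objectives: the primary hypothesis is that "depression and anxiety will significantly improve or be maintained in the four intervention worksites at the primary endpoint", relative to the active control worksites.
- Sample size calculation: alpha is 0.05/4 = 0.0125, one-tailed, because four tests are planned, each of a programme against control.
- Statistical analysis, main model: it will "test the effects of each intervention compared with the control at the 6-, 12-, and 18-month follow-ups". The term that carries the result is described with a two-valued group variable: "The interaction effect of the group (1 = intervention, 0 = control) by time will be considered an indicator of the intervention effect".
- Statistical analysis, secondary outcomes: continuous outcomes follow the same method. Turnover in each intervention group is compared with control by logistic regression.

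**The one comparison across all arms.** Completion rates and implementation scores are compared among the five arms by analysis of covariance. These are process measures, not effectiveness outcomes.

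**The concern.** The article states a comparative purpose and then fixes the number of tests, the alpha split and the group coding so that each effectiveness result is a contrast with control. Four such results do not show how far apart two programmes are. The interval for A minus B cannot be read off the two intervals against control, because both estimates share the control arm and are correlated. If one programme is significant against control and another is not, that does not show that they differ.

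At stake is the use of the results by employers. A table of four effect sizes invites ranking. Without an interval for each difference, the reader cannot tell a real lead from chance.

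**Working it through.** **Inputs from the article.** Sample size calculation: d = 0.20 against control for all four programmes; one-tailed alpha 0.0125; power 0.80; average cluster size 130; planning ICC 0.05; ICC 0.013 in the cited cohort; 28 worksites and 3,640 employees per arm. Statistical analysis: SD of K6 change 4.16.

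**Assumption.** The article gives no expected difference between programmes. Values of d from 0.05 to 0.20 are my assumption.

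**Step 1. Reproduce the stated sample size.**
- Two-sample t test, d = 0.20, one-sided 0.0125, power 0.80: 477 per arm.
- Design effect: 1 + (130 − 1) × 0.05 = 7.45.
- 477 × 7.45 = 3,553.65, rounded up to 3,554, as stated.
- 3,554 / 130 = 27.3, set to 28 worksites; 28 × 130 = 3,640; × 5 = 18,200.

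The sizing is correct for its purpose. It gives all four programmes the same d, so it contains no difference between programmes to detect.

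**Step 2. Precision of a between-programme difference.** SE = sqrt(2 × design effect / 3,640), in SD units. The pointwise half-width is 1.96 × SE. With Bonferroni over 4 × 3 / 2 = 6 pairs the multiplier is 2.638.

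| ICC | Design effect | SE | 95% half-width, pointwise | Half-width, Bonferroni |
|---|---|---|---|---|
| 0.05 | 7.45 | 0.0640 | 0.125 | 0.169 |
| 0.013 | 1 + 129 × 0.013 = 2.677 | 0.0384 | 0.075 | 0.101 |

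At SD 4.16, the pointwise half-widths are 0.125 × 4.16 = 0.52 and 0.075 × 4.16 = 0.31 K6 points.

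**Step 3. Power for a between-programme difference.** Two-sided, normal approximation: Φ(d/SE − z) + Φ(−d/SE − z), with z = 1.96 (alpha 0.05) or 2.638 (alpha 0.05/6).

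| Assumed d | ICC 0.05, alpha 0.05 | ICC 0.05, alpha 0.05/6 | ICC 0.013, alpha 0.05 | ICC 0.013, alpha 0.05/6 |
|---|---|---|---|---|
| 0.05 | 0.12 | 0.03 | 0.26 | 0.09 |
| 0.10 | 0.35 | 0.14 | 0.74 | 0.49 |
| 0.15 | 0.65 | 0.38 | 0.97 | 0.90 |
| 0.20 | 0.88 | 0.69 | 0.999 | 0.995 |

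The smallest difference detectable with 80% power is (z + 0.842) × SE. At ICC 0.05 this is 0.18 unadjusted and 0.22 adjusted. At ICC 0.013 it is 0.11 and 0.13.

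**Step 4. What a ranking could show by chance.** I simulated the planning assumption: all four programmes truly at d = 0.20, shared control, one-sided 0.0125. At ICC 0.05, about 39% of trials give a mixed result, with some programmes significant and others not, although none differs. The mean gap between the largest and smallest estimate is 0.09 SD. At ICC 0.013 the figures are about 0.5% and 0.06 SD.

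**Limits.** The calculations ignore unequal cluster sizes, attrition and baseline adjustment.

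**The case against.** The case against has several strands, and part of it stands.

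- **The claim can be read modestly.** Comparing the four interventions with the same control group may mean only that four effects are estimated in one trial on a common scale. That does answer the Background's complaint about separate samples, and it supports a descriptive ranking. It does not supply the uncertainty of a difference, which a choice between programmes needs.
- **Identifying the best programme is not a formal objective.** This stands. A reader might infer that the trial has committed itself to naming a winner and must fail. The documents do not support that: the objective, hypothesis, alpha and sample size all concern contrasts with control and agree with each other. The mismatch is with the Background and the Strengths claim.
- **Pairwise contrasts could sit in an analysis plan that is not shown.** They could, and their absence alone would be no finding. The point rests on the article promising a comparison while itself describing only tests against control.
- **The 1/0 coding does not rule out a single five-arm model.** This is correct. It may describe one indicator per arm, from which the contrasts follow directly. The randomised data allow them; they are just not planned.
- **No misuse of p-values is proposed.** This is also correct. A reader might infer that the investigators will treat significant against non-significant as evidence of a difference. Nothing in the article says so, and effect sizes are planned. The simulation shows what a reader of the results could mistake, not what the investigators intend.
- **Low power is not a given.** At the cohort ICC of 0.013 the contrasts are fairly informative. The article also says that larger effects were reported for work environment improvement and physical activity, so gaps above 0.10 are possible.

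**Conclusion.** The point holds as a mismatch between a comparative claim and analyses that are all against control. The plan allows four effects to be ranked descriptively, but gives no measure of uncertainty for any of the six between-programme differences on an effectiveness outcome.

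Precision depends mainly on the ICC, and the power figures also on the assumed difference. At ICC 0.05, multiplicity-adjusted contrasts could reliably separate only programmes about 0.22 SD apart, which exceeds the whole effect assumed against control. At ICC 0.013 the figure is about 0.13 SD. A stronger conclusion, that the trial cannot compare its programmes at all, is not supported: the data permit the contrasts, and process and implementation outcomes are already compared among all arms. The primary hypothesis, its alpha and its sample size are untouched. The change is worth making before results are seen, but it is not critical.

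**What to change.** 1. Fit one model with arm as a five-level factor by time, keeping worksite and the stratification covariates as planned. The four contrasts with control remain primary.
2. Name a secondary analysis: the six between-programme differences in K6 with simultaneous 95% CIs at 6 months, and at 12 and 18 months as for the main model.
3. State the expected precision beside it, with the ICC values and any assumed difference labelled as assumptions.
4. In Strengths and limitations, limit the claim to effectiveness against a shared control, plus whatever between-programme differences these intervals support.

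The cost is a few extra contrasts from the same data and a softer sentence. The downside is that many of the pairwise intervals may be inconclusive, particularly if the ICC is near 0.05. If the investigators do not want the contrasts, the alternative is to confine both the Background rationale and the Strengths claim to effectiveness against control.
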